## Abstract

**Background:**

People who have undergone anterior cruciate ligament reconstruction have an increased risk of osteoarthritis. Abnormality of lower limb kinematics will occur after the operation. This may be related to lower limb muscle strength, the co-excitation of hamstrings and quadriceps femoris, and the weakness of proprioception. Proprioceptive training can improve the proprioception of lower limbs and promote the recovery of lower limb kinematics. Our research objective is to observe whether proprioceptive training can improve the proprioception of lower limbs within 3 months after surgery and whether the recovery of proprioception can correct the abnormal lower limb kinematics. The secondary objective is to explore the underlying mechanism of postoperative lower limb gait abnormalities.

**Methods/design:**

This study is a prospective single-center randomized clinical trial to be conducted in the Sports Medicine and Orthopedics of Zhongda Hospital Southeast University. Forty participants aged 18–50, preparing to undergo anterior cruciate ligament reconstruction, and initial anterior cruciate ligament reconstruction using hamstring tendons as grafts will be randomly assigned to the intervention or comparator group. People in the intervention group will add proprioceptive training three times a week, 20 min each time. The intervention will be conducted on the first day after surgery. The researcher mainly collects the data of joint of sense, gait, and plantar pressure. The assessment will be divided into three stages: after signing the informed consent form (within 2 weeks before surgery), 6 weeks after surgery, and 12 weeks after surgery.

**Discussion:**

The main purpose of our study is to explore whether the proprioception of patients after anterior cruciate ligament reconstruction is weakened, whether the lower limb kinematics is abnormal and whether the lower limb kinematics can be corrected through proprioceptive training.

**Trial registration:**

Chinese Clinical Trial Registry ChiCTR2200065808. Registered on 15 November 2022; Version 1.

**Supplementary Information:**

The online version contains supplementary material available at 10.1186/s13063-023-07759-2.

## Introduction

### Background and rationale {6a}

After anterior cruciate ligament reconstruction (ACLR), the incidence of osteoarthritis is higher than that of healthy people [1–4]. According to the known research, it may be related to postoperative gait abnormalities [5]. Within one year after the operation, the biomechanics of knee joint gait can’t return to the normal mode, characterized by the reduction of the peak knee joint flexion angle, the reduction of knee joint flexion and extension moment, and the reduction of the peak vertical ground reaction force [6]. This may be caused by the weakness of quadriceps femoris muscle strength, the co-excitation of hamstrings and quadriceps femoris, and the weakness of proprioception. Some studies have found that the symmetry of quadriceps strength among people who have completed recovery training after ACLR has nothing to do with the ongoing asymmetry of gait biomechanics. After reaching the previous strength threshold of the quadriceps femoris, simply strength exercises may not improve gait asymmetry [7]. Proprioception is an important part of neuromotor control, which can accurately detect the movement and position of joints. The central nervous system receives signals from proprioceptors at joints, muscles, and tendons which send feedback to joints and muscles for muscle control. A study has found that the proprioception of patients with ACLR is weakening after surgery [8], which affects the kinematics of the knee joint of the lower limb [9, 10]. But some studies have found that no significant differences in proprioception were found between unaffected and affected legs of patients with ACLR [11]. It is possible that the proprioception disorder after surgery occurs in both lower limbs, not just the surgical side as previously thought [12].

Based on previous studies, we have hypothesized proprioceptive training added to routine rehabilitation training is more effective for the recovery of lower limb gait and plantar pressure.

### Objectives {7}

This study aims to demonstrate (1) the effectiveness of proprioceptive training on the restoration of knee joint proprioception and (2) if proprioceptive training can promote the restoration of lower limb kinematics.

### Trial design{8}

This trial is a single center, single-layer (the experimental group and the comparator group were randomly assigned in a 1:1 balanced manner), and the evaluator was blind.

## Methods: participants, interventions, and outcomes

### Study setting {9}

The study was conducted in the Sports Medicine and Orthopedics of Zhongda Hospital Southeast University in Nanjing from January 2023 to June 2024. Data management will be conducted before the intervention, 6 weeks after the intervention, and 12 weeks after the intervention (Fig. 1).

**Fig. 1 Fig1:**
[figure not shown]
Study design diagram

### Eligibility criteria {10}

#### Inclusion criteria

Aged 18–50.From March 2022 to March 2024, preparing to undergo anterior cruciate ligament reconstruction in the Sports Medicine and Orthopedics of Zhongda Hospital Southeast University.Initial anterior cruciate ligament reconstruction using hamstring tendons as grafts.

#### Exclusion criteria

Insufficient range of motionPostoperative complications such as knee stiffness and infectionAnterior cruciate ligament rupture for more than 1 monthOther diseases affecting gait: chronic ankle instability, scoliosis, etc.Accompanied by injury of articular cartilage and other ligaments

#### Patient public involvement

Patients are selected based on inclusion criteria by a member of the study, who reads their medical records on a computer upon admission. Afterwards, another research member will provide the invitation information and participant information pamphlet to the patient, and the patient will respond within 2 weeks before the surgery. The invitation message will clearly state that patients are obligated to participate in the study and will not pose a threat to subsequent treatment regardless of whether they participate or not.

After the patient voluntarily joins, they can contact the researchers on the invitation information, meet in the orthopedics department, raise questions related to the experiment, and sign an informed consent form. Then, the evaluator conducts a baseline assessment.

Patients who refuse or do not contact the researchers on the invitation information are considered to not want to participate in the study.

### Who will take informed consent? {26a}

When the patient passes the qualification screening, the informed consent form will be signed within 2 weeks of being included in the study. Before signing the consent form, the main responsible person will be contacted and questions will be answered.

### Additional consent provisions for collection and use of participant data and biological specimens {26b}

There are no ancillary studies, since they do not need additional consent provisions for collection and use of participant data and biological specimens.

## Interventions

### Explanation for the choice of comparators{6b}

This program is designed by enhanced recovery after surgery and the latest evidence-based researches. Patients’ functional activities can recover faster and improve the quality of life.

### Intervention description {11a}

The comparator group receives routine rehabilitation training after surgery, which is the first option for ACLR (Table 1). The intervention group program adds proprioceptive training on the basis of routine rehabilitation training, three times a week, 20 min each time. The intervention will be conducted on the first day after surgery.

**Table 1 Tab1:** The routine rehabilitation training

Focus on functional training
1. Jogging training, 10 min
2. Single-leg squat exercise, three series of 10 repetitions
3. Jump training, three series of 10 repetitions
4. Strength exercise of quadriceps femoris, 70–80% 1RM (1 repetition maximum), two series of 8–12 repetitions

Proprioceptive program: ① The therapist ties the mobile phone with the software to measure the flexion angle of the joint above the patient’s lower leg. Participants take a supine position with eyes closed and the therapist passively flexes the knee joint on the operative side of the participants to any angle. Participants will be asked to repeatedly bend to this angle, three series of 10 repetitions, per angle. Three angles are randomly set(5 degrees of error); ② The therapist ties the mobile phone with the software to measure the flexion angle of the joint above the patient’s lower leg. Participants take a sitting position with eyes closed. Patients actively extend the knee joint to any angle. Participants will be asked to repeatedly bend to this angle, three series of 10 repetitions, per angle. Three angles are randomly set (5 degrees of error).

#### Surgical methods

After the anesthesia took effect, the patient took a flat lying position. Placed the tourniquet on the left femur to be inflated for standby, and carried out a physical examination under anesthesia. The Lachman test and the axial shift test of the knee joint were positive. The valgus stress test was negative. The lower limb on the surgical side was routinely disinfected and covered with a towel. Then connected to the arthroscopic system. Surgeons performed lower limb blood evacuation and put on an electric tourniquet. Then set the pressure at 260 mmHg. Making a small incision on the medial side of the tibial tubercle separated the gracilis and semitendinosus tendon. Surgeons took off the tendon with a tendon extractor and weaved it into 4 strands of the transplanted tendon for standby. The arthroscopic exploration and operation channel on the operative side of the knee was established routinely to detect the rupture of the anterior cruciate ligament, removing part of the residual end of the anterior cruciate ligament and retaining part of the residual end. The femoral tunnel was established through the anterior internal auxiliary approach, and the tibial bone tunnel was established under the guidance of the locator. According to the diameter of the transplanted tendon, the tibial and femoral bone tunnels were established, and the tendon was introduced. The femoral side was fixed with the overturned steel plate and the interface compression screw, and the knee joint was moved. The tibial side was fixed by squeezing screws, and the tibial side was drilled and suspended at the distal end of the tunnel. Under the microscope, it was confirmed that the tendon was fixed reliably. The articular cavity was washed, cleaning debris, and a drainage tube was placed.

### Criteria for discontinuing or modifying allocated interventions {11b}

The intervention will be discontinued when there is unbearable knee pain or ligament rupture again and the patient’s exercise frequency is less than 80%.

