### Relevant concomitant care permitted or prohibited during the trial {11d}

In order to make the patients receive the same rehabilitation as possible within 3 months after surgery, the early rehabilitation training is printed and taken home after discharge (Table 2). Participants will be informed that rehabilitation interventions, other than those that will be received during the period of the study, will not be allowed.

**Table 2 Tab2:** The early rehabilitation training

**Stage**	The early rehabilitation training
0–3 weeks	1. Using fascial knife to reduce swelling, 5 min 2. Moving patella, 2 series of 10 repetitions 3. Flexing knee joint (0–90°), three series of 10 repetitions 4. Straightening the knee joint to the level of the healthy side 5. Straight leg raising (SLR), three sets of 10 reps 6. Glute bridge, three sets of 10 reps 7. Walking with crutches
3–6 weeks	Besides the above scheme: 1. Increasing the flexion angle of the knee joint to achieve a full range of activities in 6 weeks 2. Gradually reducing the use of crutches, and do not use braces and crutches when walking for 6 weeks 3. The resistance can be increased when the straight leg is raised 4. Step up exercise 5. Intensive exercise of vastus medialis
6–12 weeks	If the above actions have been completed easily, go to the next step (pay attention to the training intensity in 8–10 weeks, and the ligament strength in the remodeling period is insufficient), and focus on flexibility training: 1. Squat training against the wall 2. Abduction training of muscles around the hip 3. Power bicycle training 4. Stair down training (after 10 weeks) 5. Seat squatting training

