
#### Secondary outcomes

Surface electromyography: The surface electromyography signal is collected synchronously with the three-dimensional gait analysis system. The specific operation is as follows: ① On the wireless surface electromyography control terminal, select 8 muscles on both sides, including rectus femoris, biceps femoris, anterior tibial muscle, and gastrocnemius muscle; activate the wireless surface electromyography electrode; pair it with the control terminal through wireless wifi; and set the wireless channel of the relevant muscles in sequence. ② Place the common monitoring electrode at the thickest position of the abdomen of the relevant muscles of the lower limbs, parallel to the direction of the muscle fibers. Finally, install the surface electromyography electrode on the electrode piece. ③ Set the signal acquisition mode to “remote” mode. At the same time of three-dimensional gait analysis, the system will automatically record the original myoelectric signals of the relevant muscles synchronously, and automatically transmit the myoelectric data from the control end to the computer after the acquisition and save it to the database of three-dimensional gait analysis. The original surface EMG signal is processed by the righting and de-blurring provided by the software. The derived data include original data, root mean square amplitude (RMS), activation period (ACTI), integral EMG, and median frequency. The electromyographic signals were smoothed and filtered using Noraxon MR3 software, rectified and bandpass filtered (10–500 Hz). Data was exported to Excel and was time normalized. The data was calculated using Mat Lab 2020 software and Excel 2016 software.Isokinetic muscle strength test: Isokinetic muscle strength is measured on the peak moment of knee flexion and knee extension (Biodex™, USA) at the angular velocity of 30 degrees/s and 90 degrees/s.Lysholm score is a rating system in the evaluation of knee ligament injuries and is comprised of 8 tissues, of which the patient can achieve a maximum score of 100 [16]. The content includes limp (5 scores), support (5 scores), locking (15 scores), instability (25 scores), pain (25 scores), swelling (10 scores), stair-climbing (10 scores), and squatting (5 scores). Above 91 points is excellent; 84–90 points is good; 65–84 points is fair, and less than 65 points is poor.Thigh circumference is using a tape measure to measure the circumference of the thigh at 10 cm above the patella.

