### Sample size {14}

Using the G Power 3.1.9.7 software, previous studies showed that between the proprioceptive training group and the comparator group, the effective amount of JPS joint position perception difference *d* = 0.97 [13]; According to power = 80%, alpha = 0.05, and *d* = 0.97, the required sample size *n* = 36 is calculated. Considering the loss of 10% sample size, 40 subjects are required.

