## Oversight and monitoring

### Data monitoring {21a}

Because the intervention protocol is of low risk, a data monitoring committee is not necessary in this trial. The research team is in charge of reporting immediately to the leading researcher about any accident.

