### Adverse event reporting and harms {22}

Adverse reactions include ligament rupture again, patients receiving other rehabilitation intervention programs midway, or patients unwilling to continue training because of slow functional recovery, patients will be rejected and the project will be terminated.

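### Section {22} lists a protocol deviation and a withdrawal as adverse reactions, and {11b} can be read as stopping training for unbearable knee pain only when exercise frequency is low

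*Protocol article*

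**What the plan says.** Two sections of the protocol article deal with patients who stop or leave.

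- **{22}, adverse events and harms.** It opens "Adverse reactions include ligament rupture again, patients receiving other rehabilitation intervention programs midway" and continues with "patients unwilling to continue training because of slow functional recovery, patients will be rejected and the project will be terminated".
- **{11b}, discontinuation.** "The intervention will be discontinued when there is unbearable knee pain or ligament rupture again and the patient’s exercise frequency is less than 80" per cent.

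Three other sections bear on these. Section {11d} tells participants that "rehabilitation interventions, other than those that will be received during the period of the study, will not be allowed". Section {21a} plans no data monitoring committee and states that "The research team is in charge of reporting immediately to the leading researcher about any accident". Section {18b} keeps every participant in the allocated group for analysis, whether or not training was completed.

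**The concern.** A harms section should define events that injure the patient. Here the label of adverse reaction also covers a breach of the concomitant-care rule and a patient's decision to stop. If the trial team records events as {22} is printed, the resulting count cannot be read as a safety result, because some entries say nothing about injury.

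The discontinuation rule joins two clinical events and an adherence threshold with one *or* and one *and*, without grouping. Because *and* introduces a new full clause, the sentence can be taken to require low exercise frequency before either clinical event stops training. A patient with unbearable knee pain who trains as prescribed would then carry on. Training begins the day after surgery ({11a}) and there is no monitoring committee, so the written criterion is one of the main safeguards and should have only one reading.

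**Working it through.** **Step 1. The plan's own figures.** Section {14} gives d = 0.97, power 80% and alpha 0.05, hence 36 participants, then "Considering the loss of 10% sample size, 40 subjects are required". A two-sample t-test with 1:1 allocation (two-sided alpha assumed) needs 17.70 per arm, so 18 per arm and 36 in total, with power 80.7%. Allowing for loss, 36 / (1 − 0.10) = 40. Both figures reproduce, and neither depends on {11b} or {22}.

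**Step 2. The items named in {22}.**

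| Named as an adverse reaction | What it is | Basis |
|---|---|---|
| Graft re-rupture | Harm | Injury to the operated knee |
| Taking up outside rehabilitation | Protocol deviation | Not permitted under {11d} |
| Refusing to go on because recovery is slow | Withdrawal | The patient's decision; no injury described |

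Two of the three are not harms. This does not depend on how {11b} is read.

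**Step 3. The possible readings of {11b}.** Let P = unbearable knee pain, R = re-rupture, F = exercise frequency below 80%. The eight combinations were evaluated under three groupings. In four of them all readings agree: none of the three present (continue), and P with F, R with F, or all three (stop). The other four are:

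| Situation | (P or R) and F | P or (R and F) | P or R or F |
|---|---|---|---|
| P alone | continue | stop | stop |
| R alone | continue | continue | stop |
| P and R, frequency 80% or more | continue | stop | stop |
| F alone | continue | continue | stop |

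**Step 4. Does another section settle these?**

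- Both rows with R: yes. Section {22} removes a patient with re-rupture and sets no condition on exercise frequency.
- P alone: no. Outside {11b}, pain appears only as a Lysholm item, "instability (25 scores), pain (25 scores), swelling (10 scores" points), with no stopping consequence. Section {21a} concerns reporting an accident, not stopping training. Sections {18b} and {20c} concern analysis.
- F alone: both literal groupings say continue. It becomes a trigger only if the sentence is a loose list of three.

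What remains is one clinical case, pain at adequate frequency, whose answer changes between the two literal groupings. There is also a weaker adherence case, whose answer changes only under the list reading.

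**The case against.** The best defence of {11b} is that a list of three separate triggers was intended. The section is where such a list belongs, the article's English is loose throughout, and to keep training a knee in unbearable pain because the patient trains often makes no clinical sense. This is probably right, and it limits the point to wording. It does not remove it: the sentence does not say what was meant, and the list reading would also make low frequency alone end training, which neither literal grouping does.

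For {22}, the defence is that the section works mainly as a list of reasons for removal under a poor label, and that re-rupture, being named separately, can still be reported alone. That is fair, and it is why the consequence is conditional on someone counting adverse reactions as {22} lists them. It is also fair that the article condenses a full protocol, offered on request under {31c}, which may hold clearer instructions. That does not excuse wording that is printed and wrong.

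A reader might infer more than the text supports, in four ways:

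- *Staff have no instruction to stop for pain.* This is true under only one of the three groupings.
- *A given session count marks the unprotected patients.* Exercise frequency is not defined. The schedule of "three times a week, 20 min each time" belongs to the added training only, and the weekly check-in in {11c} would suit a weekly measure equally well. Any session count would merely restate 80%.
- *The safety rate is inflated by a known amount.* The planned loss is 0.10 × 40 = 4, and 4/40 is 10 percentage points. To use that as the size of the problem, one must assume that all losses have these two causes and that the three items are pooled into one rate. The article plans no such rate.
- *Leaving pain out of {22} is an error.* The section says that adverse reactions include the named items, so its list is not exhaustive.

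**Conclusion.** The point holds as a minor defect in two separate places. In {22}, two of the three named adverse reactions are misclassified, and {11d} itself shows that one of them is a deviation. In {11b}, one literal reading makes stopping for unbearable pain depend on exercise frequency below 80%, and nothing else printed in the article corrects it.

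The conclusion on {22} assumes only that events are recorded as the section lists them. The conclusion on {11b} is that the text is ambiguous; it does not claim that the unsafe reading was intended or will be followed. It also takes the removal described in {22} to settle re-rupture.

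No sample size, alpha, power or efficacy estimate is affected, and analysis by allocated group is already stated in {18b}. What is at stake is safe conduct and a harms count that can be interpreted.

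**What to change.** **{11b}:** state that unbearable knee pain and ligament re-rupture each stop training on their own, whatever the exercise frequency. Give frequency below 80% as a separate adherence criterion, and say whether it stops training or is only recorded.

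**{22}:** record re-rupture and unbearable knee pain as adverse events. Count outside rehabilitation as a protocol deviation and unwillingness to continue as a withdrawal, each separately from harms.

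**Cost:** rewording of two short sections, and separate fields for adverse events, deviations and withdrawals in the data spreadsheet. There is no effect on the number of participants or on the planned analysis.
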